### Randomization, allocation and blinding

Participants are enrolled by the RA. A computer-based randomization system (Sealed Envelope, London, UK) is used to allocate participants in a 1:1 ratio to either experimental or control groups, using permuted blocks while maintaining concealment. The research physiotherapist (PT) accesses the system immediately after the participant is enrolled; the allocation is provided immediately. The only person blinded to treatment allocation is the RA, who performs the outcome measures. The research PT is blinded to the results of the outcome measures. If the participant is undergoing rehabilitation during the study period (for example, outpatient or community-based rehabilitation), the rehabilitation professional is informed of their patient’s participation in the study, to ensure that the home-based exercise is compatible with the participant’s therapy. The PT will reveal a participant’s allocation in the case of serious adverse effects.

### Interventions

VRT in the experimental group is provided using Jintronix Rehabilitation software (Jintronix, Montreal, Canada). A Kinect camera (Microsoft Canada Co., Mississauga, Canada) captures the movements of the participant using infrared technology and allows him or her to control an avatar, which interacts with an activity presented on a TV screen (Fig. 1a). Several games and activities are available to train participants in standing balance (e.g. moving a ball along a maze, slalom skiing), reaching (e.g. putting dishes away), stepping (e.g. stepping onto tablets placed in a circle, whack-a-mole), gentle strengthening (e.g. standing hip abduction, arm circles, sit-to-stand) and aerobic exercises (e.g. marching on the spot). Game and activity difficulty can be increased by requiring more repetitions or greater speed, distance and/or accuracy. Specific games and activities, and their parameters are selected for each participant based on his or her physical abilities, fall risk, rehabilitation goals and tolerance.

**Fig. 1 Fig1:**
[figure not shown]
**a** Experimental intervention – home-based virtual reality training targeting standing balance, stepping, reaching, strengthening and aerobic exercise. **b** Control intervention – iPad apps targeting cognition and hand fine motor control

Participants in the control group are provided with an iPad (Apple Canada, Toronto, ON), which contains a selection of apps suited for memory and cognition (e.g. Unblock Me, Fill Wooden Blocks, iSays, Stroop Effect, iOT session, Sudoku, crossword), visual scanning and tracking (e.g. iOT session), and fine motor skills (e.g. writing practice, iOT session, 5 Tiles, Dexteria, Tap Tap Dash, Ball Maze, Fruit Ninja, Finger Smash) (Fig. 1b).

### Outcome measures

To address each primary objective as numbered, the following outcome measures are used:The number of participants recruited over 18 months will be determined relative to the number who met the study participation criteria and the number who were approached by the clinical staff and the RA. The inability to recruit at least 30 participants will require the researchers to alter recruitment procedures for a definitive RCT.Ability to comply with the research protocol will be assessed through notes taken by the research PT and comments provided by the participant and study partner in the log book, on the phone and at the interview. If a majority of participants perform less than 450 min of VRT over the 6 weeks (900 min is the requirement of the protocol), the use of VRT as a motivation to encourage people to exercise post stroke will be reconsidered and reasons why will be discerned. Retention of participants will be measured and a loss of more than 25% will suggest that changes should be made to the protocol.The presence of adverse effects will be recorded from telephone conversations with the participant and through the log book. The occurrence of major adverse effects (e.g. falls with serious injuries) would suggest that home-based VRT, as used in this protocol, is too risky to continue.Ability to use VRT in the home will also be assessed through comments written in the log book or made by the participants during VRT installation and follow-up phone calls and in the interview. Use and progression of the VRT program will be monitored asynchronously by the research PT. Poor learning would be implicated if no progression is observed. Also, expressions of frustration or confusion with the games will indicate poor ability to do VRT.Acceptability of VRT will also be assessed using information gleaned from the log books and follow-up phone calls and from the Physical Activity Enjoyment Scale, which rates (from 1 to 7) 18 statements of one’s feelings about physical activity (PACES) [20], administered at the post hoc assessment only.Costs related to the VRT equipment/licences, travel and salaries will be calculated, in order to prepare a budget for a definitive RCT.

The following outcomes will be used to address each secondary objective.The first secondary objective (feasibility and acceptance of a battery of outcome measures) will be assessed by recording the completion of 11 outcome measures, including physical outcomes (5 tests), questionnaires (4 in total), a log book and a semi-structured interview. The inability of all participants to complete the outcome measures, within a reasonable time frame (2 h) will result in re-thinking the use of each measure in a definitive RCT.The potential for VRT to maintain or improve standing balance, gait, general function and community integration post stroke will be assessed with the following tests:Berg Balance Scale (BBS) [21]. The BBS tests balance and mobility using 14 items scored from 0 to 4.Timed Up And Go (TUG) [22–24]. The TUG assesses the time required to stand up, walk 3 m, return and sit down. There are 3 versions, original, manual (performed while holding a cup of water) and cognitive (performed while also doing a cognitive task).Five Times Sit-To-Stand Test (FTSST) [25]. The FTSST tests the time it takes to stand up from a chair and sit down again five times.Community Balance and Mobility Scale (CB&M) [26]. The CB&M assesses more difficult balance tasks that are relevant to community ambulation.Quantitative analysis of quiet stance and limits of stability in standing [27]. These tests provide quantitative information about the neural mechanisms of postural control [1].Stroke Impact Scale (SIS) [28]. The SIS assesses health status after stroke.Reintegration to Normal Living Index (RNLI) [29]. The RNLI assesses the degree to which individuals have reintegrated back into normal social activities after illness. It has acceptable reliability and validity.

All of these scales have adequate to excellent reliability, validity and responsiveness to change (except responsiveness to change for the FTSST) [26, 28, 30–36].The Motivation for Physical Activity Questionnaire will be administered before the VRT protocol only, to better describe the participant sample [37].3.The results of the BBS will be assessed and used to calculate an effect size in order to estimate the sample size for a definitive RCT.

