**Methods:**

Forty patients who can stand for at least 2 min and are soon to be discharged from inpatient or outpatient rehabilitation post stroke are being recruited in Ottawa, Canada and being randomized to control and experimental groups. Participants in the experimental group use home-based VRT to do rehabilitative exercises for standing balance, stepping, reaching, strengthening and gentle aerobic fitness. Control group participants use an iPad with apps selected to rehabilitate cognition, hand fine motor skills and visual tracking/scanning. Both groups are instructed to perform 30 min of exercise 5 days a week for 6 weeks. VRT intensity and difficulty are monitored and adjusted remotely. Weekly telephone contact is made with all participants. Ability to recruit participants, ability to handle the technology and learn the activities, compliance, safety, enjoyment, perceived efficacy and cost of program delivery will be assessed. A battery of assessments of standing balance, gait and community integration will be assessed for feasibility of completion within this population and potential for improvement following the intervention. Effect sizes will be calculated.

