**Trial Registration:**

ClinicalTrials.gov, NCT03261713. Registered on 21 August 2017. Registration amended on 1 June 2018 to decrease enrollment from 40 to 20 due to a cut in study funding and difficulty recruiting participants.

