### Sample size and recruitment

No sample size calculation was performed as this is a feasibility trial. The sample size of two groups of 20 is based on available time and recruitment expectations and funding level. It is expected that having 20 participants in the VRT arm of the study will be enough to discern the feasibility of home-based VRT. It is deemed reasonable that 40 out of the estimated 375 stroke rehabilitation inpatients and the 375–450 patients who attend outpatient stroke rehabilitation over 18 months will be eligible and interested in the study. Members of the clinical care team will be made aware of the study through their clinical manager and attendance at team meetings. The study will be stopped prematurely if serious adverse effects occur.

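### Enrolment was cut from 40 to 20, but the abstract, the sample-size rationale and the recruitment threshold of 30 still describe the 40-patient design

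*Protocol article*

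**What the plan says.** The abstract's Trial Registration paragraph gives the latest enrolment figure: "Registration amended on 1 June 2018 to decrease enrollment from 40 to 20 due to a cut in study funding and difficulty recruiting participants".

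Three other places keep the larger design:

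- Abstract, Methods, in the present tense: "Forty patients who can stand for at least 2 min and are soon to be discharged".
- Methods, Sample size and recruitment: "The sample size of two groups of 20 is based on available time and recruitment expectations and funding level". The section then rests the feasibility assessment on the size of one arm: "It is expected that having 20 participants in the VRT arm of the study will be enough to discern the feasibility of home-based VRT".
- Methods, Outcome measures, for primary objective 1: "The inability to recruit at least 30 participants will require the researchers to alter recruitment procedures for a definitive RCT".

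The sentence just before that threshold sets out how recruitment will be measured: "The number of participants recruited over 18 months will be determined relative to the number who met the study participation criteria", and also relative to the numbers approached by clinical staff and the research associate.

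The Introduction and the randomization section both give 1:1 allocation. The Participants section dates the start of recruitment to May 2017. The article was published on 7 June 2019, a year after the amendment.

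**The concern.** The article gives two enrolment figures and does not say that one replaces the other in the design sections. The later figure undoes two statements that depend on the earlier one.

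First, the only rationale for the sample size is that 20 in the VRT arm suffices. The article also says that the size of two groups of 20 rests partly on the funding level, and funding is what was cut. The rationale therefore describes a trial that is no longer being run.

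Second, the recruitment threshold is a count above the new ceiling. Estimating the recruitment rate is primary objective 1, and the Discussion says this rate will inform the proposal for the definitive trial. A count that cannot be reached cannot distinguish fast recruitment stopped by lack of money from slow recruitment.

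**Working it through.** **Inputs.** Enrolment before and after amendment: 40 and 20 (Trial Registration). Arm size: 20 (Sample size and recruitment). Threshold: 30, over 18 months (Outcome measures). Allocation: 1:1 (Randomization, allocation and blinding). Annual intake: about 250 inpatients and 250–300 outpatients (Participants). The article states that no sample size calculation was made, so there is no power figure to reproduce.

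**1. The pre-amendment plan is consistent with itself.**

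- Total: 2 × 20 = 40.
- Pool over 18 months: 250 × 1.5 = 375 inpatients; 250 × 1.5 = 375 to 300 × 1.5 = 450 outpatients. Both match the stated figures.
- Threshold: 30/40 = 75% of target, so it could be met or missed.

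**2. With the amended enrolment it is not.**

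- Threshold: 20 < 30, a shortfall of 10 even with full enrolment. The result is the same whether the 20 enrol in 6 months or in 18.
- VRT arm: 20/2 = 10, against the 20 stated. The permuted-block size is not given. If it lies between 2 and 10 (an assumption), an incomplete last block could put the arm anywhere from 8 to 12.

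**3. What the smaller arm means for the compliance criterion.** Whether a majority of participants reach 450 min is read from the VRT arm alone. Exact (Clopper-Pearson) 95% limits for x of n are the 0.025 quantile of Beta(x, n − x + 1) and the 0.975 quantile of Beta(x + 1, n − x).

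| Observed 50% compliance | 95% CI |
|---|---|
| 10 of 20 | 27–73% |
| 5 of 10 | 19–81% |

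**4. The threshold as a rate.**

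- 40/18 = 2.22 per month (pre-amendment target)
- 30/18 = 1.67 per month (threshold)
- 20/18 = 1.11 per month (amended target, if spread over the full window)

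At the threshold rate, 20 recruits take 20/1.67 = 12 months.

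**5. The rate set against the dates.** From May 2017 to 1 June 2018 is 12 to 13 months. The number enrolled by the amendment date is not given. If the 20th participant had not yet joined, the best possible overall rate is between 20/13 = 1.54 and 20/12 = 1.67 per month. The rate would then miss the old bar or at best just meet it. It would still show by how much, which the capped count cannot.

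**The case against.** A reader might infer that primary objective 1 has failed before any data are seen, or that the recruitment assessment is void. The documents do not support this, for three reasons.

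- The cut came 12 to 13 months into an 18-month window and was partly a response to difficulty already met in recruiting. Missing 30 is therefore not purely an effect of the cap.
- Missing 30 neither stops the trial nor declares home VRT infeasible. It only requires changed recruitment procedures in the definitive trial, and the reported difficulty already points that way.
- Recruitment relative to eligible and approached patients is already planned. Those proportions do not depend mechanically on the cap.

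A reader might also infer that 10 in the VRT arm breaches a precision requirement. None is stated. The compliance criterion (a majority) and the retention criterion (25% loss) are proportions that can be applied at any n, and the safety criterion is triggered by the occurrence of major events, not by a bound on their rate. The Discussion concedes the small sample, although only for detecting differences between groups.

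It can also be said that the abstract discloses the cut and both reasons for it, so a careful reader is not misled about the current target. All of this stands and limits the consequence. It does not remove the conflict: the count of 30 is the only numerical threshold given for recruitment, and no section restates the arm size, its justification or the threshold for 20.

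**Conclusion.** The point holds as an internal contradiction with two definite effects. The VRT arm will be about 10, half the size called sufficient, and the recruitment count cannot reach 30, so its consequence follows whatever the recruitment rate and cannot separate funding from recruitability. The count still carries some information, and objective 1 does not rest on it alone.

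This assumes that 20 is kept as the ceiling on enrolment and that allocation stays 1:1, as the article states. The confidence intervals illustrate what the smaller arm can show; they are not evidence that a planned precision was missed.

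**What to change.** 1. State enrolment as 20, about 10 per arm, in the abstract's Methods paragraph and in the sample-size section.
2. Delete the sentence that calls 20 in the VRT arm enough, or restate it for about 10, for example with the 19–81% interval for an observed 50% compliance beside the 27–73% that 20 would have given.
3. Keep the count of 30 but label it as the pre-amendment threshold.
4. Judge recruitment on measures that do not depend on the cap: the proportions of eligible and approached patients already planned, and recruits per month open. Compare the monthly rate with 30/18 = 1.67. Say plainly that this re-expresses the old bar after the amendment, when recruitment was already known to be difficult, so that it is not read as a prespecified test.

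The reasons for the cut are already given in the Trial Registration paragraph and need no addition.

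The cost is wording only, with no change to conduct or data collection. The downside is that the stated size and precision become less favourable.

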### Participants

Potential participants have been recruited from the inpatient and outpatient stroke rehabilitation programs at Élisabeth Bruyère Hospital in Ottawa, ON, Canada, since May 2017. Élisabeth Bruyère Hospital is the largest provider of rehabilitation services for stroke in the Champlain Local Health Integration Network in Eastern Ontario and admits approximately 250 stroke survivors to its inpatient program and 250–300 to its outpatient program each year.

Stroke survivors are eligible for the trial if they (1) have had a stroke (ischemic or hemorrhagic) resulting in physical impairment; (2) have sufficient preserved cognitive ability to learn VRT; (3) are receiving inpatient or outpatient stroke rehabilitation services; (4) are able to stand independently for at least 2 min; (5) have a study partner who can attend two training sessions with the participant and is able to be in the home when the participant is doing VRT; (6) can read, speak and understand English; (7) live within 50 km of Élisabeth Bruyère Hospital; (8) are able and willing to attend four appointments at Élisabeth Bruyère Hospital (two for assessment, two for training); (9) will not be travelling away from home for more than 2 days a week for the duration of the study and (10) have sufficient space in their home to do VRT safely. Patients are excluded if they have an unstable medical condition, seizures or vertigo, or are unable to safely perform mild to moderate exercise. Participation in other, non-VRT exercise or rehabilitation programs post discharge does not influence their eligibility in this feasibility trial. The presence of expressive aphasia is not a definitive exclusion criterion.

Members of a patient’s circle of care (physicians, residents, nurses, physiotherapists, occupational therapists, outpatient program triage nurse and social workers or their students) screen patients for the study using the aforementioned criteria. If the criteria are met, the member of the patient’s circle of care asks the patient if he or she would like to hear about a study using video games and exercise at home. If the patient consents verbally, their name is identified to the research associate (RA), who approaches the patient and provides full details on the study. Interested patients are given an opportunity to ask questions before written informed consent is obtained.

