**Fig. 2 Fig2:**
[figure not shown]
Schedule of enrolment, interventions, and assessments

After assessment, the research PT visits the participant’s home to install the equipment and finish training. The games, safety considerations and follow-up procedures are reviewed with the participant and his or her study partner. Participants in both groups are instructed to perform their exercises five times a week for 6 weeks. VRT sessions are designed to run for approximately 30 min of activity time and participants in the iPad group are asked to use it for at least 30 min a day. This amount of additional training (15 h) has been shown to produce a significant improvement in activities of daily living post stroke [38]. The study partner must be in the home of the participant while he or she is doing VRT.

All participants are contacted by the research PT via telephone or email twice a week for the first week and at least once a week for the following 5 weeks to offer encouragement, suggest modifications to the games and identify any safety issues or technical problems. Participants are also invited to contact the research PT as needed. For those in the experimental group, the research PT monitors the compliance and success rate of VRT at least once a week using the remote access feature of the VRT system, and can modify the games if necessary.

Participants in both groups are provided with a logbook in which to record technical issues with the VR equipment, thoughts on how the games are going and if progression was required, safety concerns and adverse events and changes to the exercise environment. Those in the control group must also record the time spent on the iPad apps each day and which apps are used. Participants are encouraged to do as many activities of daily living (ADL) and instrumental ADLs as they wish, including walking, participation in exercise groups and therapy. Throughout training and during the intervention, every attempt is made to equalize contact time with the research personnel between the two groups.

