After the 6-week exercise protocol is completed, participants return to Élisabeth Bruyère Hospital for their post-intervention assessment (1½ h). During the post-intervention assessment, the physical outcome measures and community integration questionnaires are repeated, the PACES is administered and a semi-structured interview takes place with a second RA in which participants and their study partners are asked several questions about their experience with VRT (Additional file 2: Figure S2). Once outcome measures are completed the research PT visits the participant’s home for a second time to remove the equipment.

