### Data management and analysis

All data will be coded with a participant number; the code breaker will be kept in a different area on the computer server in a password-protected file. A database will be kept with demographic information (age, sex, details of stroke, medical history etc.) and the results of the physical outcome measures and questionnaires. Data on recruitment, retention, number of exercise sessions undertaken in 6 weeks and the number of minutes for each session will be included. Major and minor adverse effects will be recorded and ancillary care will be provided if required.

The pre-intervention and post-intervention scores for the BBS, TUG, FTSST, CB&M, SIS, RNLI and PACES will be reported as mean (95% confidence intervals). Missing data will be handled using complete case analysis. Each scale (except the PACES, which is assessed post-intervention only) will be compared using mixed-methods analysis of variance (ANOVA) (within-group factor, time; between-group factor, group; interaction, time x group). For quiet stance and limits of stability in sitting and standing, an ellipse encompassing 95% of the center of pressure data points will be computed. The area, anteroposterior and mediolateral dimensions of this ellipse will be determined. Results will be compared over time using mixed-methods ANOVA as aforementioned. Linear regression will be used to analyze what proportion of the results of the physical outcome measures is explained by motivation to undertake physical activity (assessed with the Motivation for Physical Activity Questionnaire and the PACES).

Recordings from the interviews will be transcribed. Qualitative data from the transcribed interviews, log books and records of contacts with the participants will be grouped, organized and classified into categories or themes [39, 40]. The categories will be examined to answer primary research objectives 2, 3, 4 and 5, and secondary objective 1 on the enjoyment of VRT, safety, difficulties with the technology or exercises and perceived effectiveness. The datasets created during this study will be available from the corresponding author on reasonable request.

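### The sources for adverse effects (primary objective 3) differ between sections and leave out the study partner, so events may be missed; one common source list would settle it

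*Protocol article*

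**What the plan says.** All references are to the Protocol article.

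- **Outcome measures, primary objective 3:** "The presence of adverse effects will be recorded from telephone conversations with the participant and through the log book". The same paragraph says that major adverse effects would mean VRT, as used here, is too risky to continue.
- **Outcome measures, primary objective 2:** compliance is judged from the research physiotherapist's (PT's) notes and from comments by both participant and study partner, in the log book, by telephone and at interview.
- **Abstract, Methods:** "Weekly telephone contact is made with all participants".
- **Procedures and participant timeline, contacts:** "All participants are contacted by the research PT via telephone or email twice a week for the first week". After that the minimum is one contact per week for five weeks, and finding safety problems is among the stated purposes.
- **Procedures and participant timeline, log book:** "Participants in both groups are provided with a logbook in which to record technical issues with the VR equipment"; it also covers safety concerns and adverse events. The partner has to be in the home during VRT.
- **Procedures and participant timeline, final visit:** a second research associate (RA) holds an interview in which "participants and their study partners are asked several questions about their experience with VRT".
- **Data management and analysis:** interviews, log books and records of contacts are sorted into themes. "The categories will be examined to answer primary research objectives 2, 3, 4 and 5"; objective 3 is safety.
- **Participants:** "The presence of expressive aphasia is not a definitive exclusion criterion". Participants must also be able to read, speak and understand English.

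**The concern.** Safety is a primary objective, and its conclusion depends on whether any major event is recorded. The article gives more than one answer to what counts as a source. An event first reported in an email, by the partner on the telephone, or at the final interview counts under one section and not clearly under another.

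The sources named in Outcome measures are also narrow for this population. They rely on the participant's own speech and a self-kept record, in a trial that may enrol people with expressive aphasia. The person most likely to witness a fall during VRT, the study partner, is not named in that sentence. The contacts are made by the research PT, who is not blinded, and the Discussion says that no adverse effects are expected from VRT. A fixed set of questions would limit the influence of that expectation.

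**Working it through.** The article gives no event rate, capture rate or safety sample size, so there is no figure to reproduce. The check is a comparison of sections, followed by an illustration of why capture matters.

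**1. Sources for objective 3, by section**

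| Source | Outcome measures (objective 3) | Procedures and participant timeline | Data management and analysis |
|---|---|---|---|
| Telephone with participant | Named | Allowed, safety is a stated purpose | Within records of contacts |
| Email with participant | Not named | Allowed, same purpose | Within records of contacts, if kept |
| Log book | Named | Both arms | Named |
| Final interview | Not named | Held; described as about VRT | Named |
| Study partner | Not named (named for objective 2) | Must be at home during VRT; interviewed | Through the interview |

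**2. How far email could replace the telephone.** Minimum scheduled contacts are 2 in week 1 plus 1 in each of the next 5 weeks: 2 + 5 = 7 per participant, the same in both arms. The procedures allow every one of these to be an email; the Abstract says telephone. If all are emails, the Outcome measures sentence taken alone leaves only the log book, whereas Data management and analysis still leaves contact records and the interview. The count depends on which section is followed.

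**3. Are the sources equal between arms?** Contact schedule, safety purpose and log book are common to both. The interview, described only in terms of VRT, may not be. Weekly remote monitoring and required partner presence are stated only for VRT, although the monitoring is for compliance and success rate. These features would tend to raise capture in the VRT arm.

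**4. Illustration: effect of capture on the any-major-event rule.** Let n be the VRT arm size, p the true risk of a major event per participant, and s the share of events captured. Then

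P(at least one recorded) = 1 − (1 − p·s)^n.

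The planned n is 20. With enrolment amended to 20 in total (Trial Registration), 1:1 allocation gives about 20/2 = 10. Neither p nor s is in the documents; both are assumed.

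| n | p | s = 1.0 | s = 0.9 | s = 0.7 | s = 0.5 |
|---|---|---|---|---|---|
| 20 | 5% | 64.2% | 60.2% | 51.0% | 39.7% |
| 20 | 10% | 87.8% | 84.8% | 76.6% | 64.2% |
| 10 | 5% | 40.1% | 36.9% | 30.0% | 22.4% |
| 10 | 10% | 65.1% | 61.1% | 51.6% | 40.1% |

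Example: 1 − (1 − 0.05 × 0.5)^20 = 1 − 0.975^20 = 0.397.

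Even with full capture, zero events gives a one-sided 95% upper bound on risk of 1 − 0.05^(1/20) = 13.9% for n = 20, and 1 − 0.05^(1/10) = 25.9% for n = 10. The rule has little information to spare.

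**The case against.** A reader might infer that events are under-counted and ascertained unequally between the arms. The documents do not support that.

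- **Under-counting is not shown.** Safety is a stated purpose of at least 7 contacts, whatever their mode, and the log book covers adverse events. Records of contacts can include emails. This stands: missed events are a risk, not a finding.
- **No between-arm comparison is planned.** Objective 3 and its decision rule concern VRT, and the analysis of variance covers scales and centre-of-pressure measures only. Better capture in the VRT arm would serve the stated objective. This stands: no bias in a stated comparison is shown. Uneven sources matter only if control-arm events are later read as background.
- **The interview guide is not shown.** It is in Additional file 2, and the article elsewhere uses VR wording for both groups, as it does for the log book. What controls are asked cannot be judged from one condensed phrase. This stands.
- **The partner is not wholly absent.** Partners comment in the log book and are interviewed, so some of their reports reach objective 3. This stands in part: the safety sentence still limits telephone reports to the participant, while the compliance sentence does not.
- **Aphasia is only not a definitive exclusion.** The language criterion and the partner are mitigations, and the article does not say that anyone with aphasia is enrolled. This stands.
- **A question script is operational detail that an article may omit.** Its absence is accordingly no fault. The stated source lists are different: they are in print and disagree.

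**Conclusion.** The point holds in a limited form. The article's source lists for a primary safety outcome are inconsistent, and the list in Outcome measures is narrower than the trial's own procedures allow. Events may be missed, particularly in participants contacted by email or with expressive aphasia if enrolled. The interview may be an uneven added source if control-arm events are used for context.

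The size cannot be estimated from the documents. The table shows only that incomplete capture would matter for a rule triggered by any major event in 20, or about 10, participants. Its low-capture columns are pessimistic for serious injuries, which are likely to surface by some route; minor events, also part of objective 3, are easier to miss. This is an inexpensive improvement worth making, not a flaw that undermines the trial.

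**What to change.** 1. Reconcile the Abstract, Outcome measures, Procedures and participant timeline, and Data management and analysis into one source list for adverse effects. Make it identical in both arms and cover telephone, email, log book and study-partner reports.
2. At each scheduled contact, have the research PT ask participant and partner the same short, fixed adverse-event questions in both arms.
3. At the post-intervention visit, have the second RA ask the same questions of both arms before the open interview. This keeps the task away from the blinded outcome assessor.
4. List events first mentioned in the open interview separately, so that counts from the common sources can be read on their own.

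The cost is a one-page script and a few minutes at contacts that already take place, with no added staff. The downside is that more events will be recorded, mostly minor ones if the questions work as intended.
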